## **Statistical methods**

All data are entered into SAS 9.3 software (SAS Institute Inc., Cary, NC, USA). The measurements will be calculated mean, standard deviation, median, quartile, minimum, and maximum. Categorical variables will describe as frequency and percentage. Changes from baseline in primary and secondary endpoints will be analyzed using a covariance pattern model, with treatment as classification variables and baseline value as a covariate. Point estimates and 95% confidence intervals (CIs) for the mean change within each treatment group, as well as for the differences in mean change between the two groups will be estimated. Differences in categorical variables will be analyzed using Pearson  $\chi^2$ , CMH  $\chi^2$  or Fisher probabilities. For primary outcomes,  $p < 0.025$  will be considered as significant. Other outcomes  $p < 0.05$  will be considered as significantly.

Adverse events (AEs) will be summarized. The incidence of adverse events will be summarized by body system organ class and preferred term. Analyses for safety and tolerability endpoints will be summarized using descriptive statistics for continuous variables or frequency counts and percentages for categorical variables. All conclusions will be based on final analysis rather than the interim analysis.

---

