### **9.3 Definitions of analysis sets**

The primary efficacy analysis population will be based on the Full Analysis Set (FAS) and the Per-Protocol Analysis Set (PP). The secondary analysis population and the safety analysis population will be based on the Per-Protocol Analysis Set (PP) and Safety Analysis Set (SS), respectively.

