## **9.4 Outcome measures for analysis**

The statistical description includes mean, standard deviation, median, quartile and maximum value and minimum value of continuous variables, and frequency and percentile of categorical variables. All data will be examined for outliers and missing values. Some variables will be transformed. Analysis will be based on the data distribution and research issues. Continuous variables will be analyzed with ANOVA for randomized block design, paired t-test and rank sum test to compare the changes from baseline within the same group. ANOVA and rank sum test will be used to examine the differences between groups for continuous variables. Categorical variables will be analyzed with Pearson chi-square test, CMH chi-square test or Fisher probabilities to compare the differences between groups. A P value of  $<0.05$  is considered to be statistically significant except for extra specification.

**Demographic and baseline characteristics:** Frequency distribution and summarized statistical data of demographic and baseline variables will be analyzed individually according to different treatment groups in efficacy analysis.

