### **9.4.1 Analysis of the primary variable(s)**

The primary endpoints in the study are absolute fasting C-peptide changes between saxagliptin + metformin (and insulin) group vs. metformin (and insulin) group, and vitamin D + saxagliptin + metformin (and insulin) group vs. metformin (and insulin) group from baseline after 104 weeks of treatment. The primary endpoint will be analyzed utilizing mixed model repeated measures (MMRM) on full analysis set (FAS). Within the framework of MMRM, point estimations and 2-sided 95% CIs will be presented at each visit for the mean change within each treatment group as well as the difference of the mean change between treatment groups. The following hypothesis will be tested to establish superiority:

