#### **9.4.2 Analysis of the secondary variable(s)**

The secondary endpoints including other parameters of  $\beta$ -cell function, for example C-peptide changes during MMTT. Glycaemic control parameters including HbA1c, FPG and PPG. Insulin-sparing effect is the difference of daily insulin dosage. One-way ANOVA will be used to examine the baseline data and the changes in AUC during MMTT, FPG, PPG, HbA1c and insulin dose between groups. The changes of secondary variables described above from the baseline within the same group and between groups will be analyzed with repeated measurement analysis of variance. The frequency counts

and percentages will be summarized on proportion of patients achieving  $\beta$ -cell function protection and glycaemic control.

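### Section 9.4.2 prescribes unadjusted ANOVA of change for secondary endpoints that the synopsis assigns to a baseline-adjusted covariance pattern model

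*Protocol*

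**What the plan says.** Three places in the protocol govern the continuous secondary endpoints.

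- **Synopsis, Statistical methods.** One model covers primary and secondary changes from baseline: "Changes from baseline in primary and secondary endpoints will be analyzed using a covariance pattern model", with treatment as a factor and the baseline value as covariate.
- **Section 9.4.2.** "One-way ANOVA will be used to examine the baseline data and the changes in AUC during MMTT", and likewise for FPG, PPG, HbA1c and insulin dose between groups. The next sentence says that changes in these variables within and "between groups will be analyzed with repeated measurement analysis of variance". No covariate, covariance structure or contrast is named.
- **Section 9.4.** A general rule for all continuous variables: "ANOVA and rank sum test will be used to examine the differences between groups for continuous variables".

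MMRM is named in 9.4.1 for the primary endpoint only. ANCOVA appears only in the LOCF sensitivity analysis of that endpoint. Section 9.3 assigns the secondary analyses to the per-protocol set.

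**The concern.** An SAP can add detail to a protocol, but it cannot follow two texts that name different models for the same endpoints. Section 9.4.2 also gives two between-group methods for the same changes without ranking them. In an open-label trial, a choice of method left open until the data are in hand is best avoided.

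The methods are not interchangeable:

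- One-way ANOVA has no covariate, so the baseline adjustment promised in the synopsis disappears.
- Across three arms it tests whether any arm differs. The secondary objectives in section 2.2 compare saxagliptin, with or without vitamin D3, with metformin (and insulin).
- Repeated-measures ANOVA in its conventional form uses only subjects with every visit, which would matter for a 104-week trial with visits at weeks 26, 52, 78 and 104.

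**Working it through.** **Sample size, to see whether it is touched.** Section 9.2 gives means of 149.2 and 108.4 (difference 40.8), SDs of 84.5 and 52.8, two-sided alpha 0.025 and 90% power.

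- Root-mean-square SD = √[(84.5² + 52.8²)/2] = 70.46.
- The protocol's formula gives 75.28, so 76 per group. Then 76/0.8 = 95, set at 100.

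The stated figures reproduce. They rest on the primary endpoint alone, so nothing below changes them.

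**Cost of dropping the baseline term.** Assume the same variance s² at baseline and follow-up, and correlation r between them. The protocol gives neither.

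- Variance of unadjusted change: 2s²(1 − r).
- Variance after adjusting for baseline: s²(1 − r²).
- Ratio, adjusted to unadjusted: (1 + r)/2.
- Extra subjects needed by the unadjusted analysis for equal precision: 2/(1 + r) − 1.

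| r (assumed) | Variance ratio (1 + r)/2 | Extra subjects |
|---|---|---|
| 0.4 | 0.70 | 43% |
| 0.5 | 0.75 | 33% |
| 0.6 | 0.80 | 25% |
| 0.7 | 0.85 | 18% |
| 0.8 | 0.90 | 11% |
| 0.9 | 0.95 | 5% |

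**Bias or imprecision?** Under the same assumptions, if the arms differ at baseline by d through chance, the unadjusted change contrast shifts by −(1 − r)d. Over repeated randomisations d averages zero, so the contrast is unbiased with complete data. What remains is extra variance and dependence on the imbalance that happens to occur.

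**Incomplete subjects, conditional on implementation.** Section 9.2 plans about 20% drop-out. With 100 per arm, a complete-case repeated-measures ANOVA could lose up to about 0.20 × 100 = 20 subjects per arm, including the visits at which they were seen, and keep about 80. An illustrative simulation assumed a true difference of 0.5 SD, four visits, and drop-out of 20–34% per arm driven by the last observed change. Completers gave 0.43–0.47 and a likelihood analysis gave 0.50. The size of that gap depends on those assumed inputs.

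**The case against.** The strongest reply is that most of this is a matter of implementation.

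- **Discarded subjects.** A reader might infer that 9.4.2 discards incomplete subjects. The protocol does not state listwise deletion, and a mixed-model fit would avoid it. The 20% is a sample-size allowance for the primary endpoint, and section 6.6 requires the Visit 26 assessments at discontinuation. The loss is therefore a possible consequence of the conventional method, not something the plan prescribes.
- **Bias.** A reader might also infer that unadjusted change biases the treatment contrast through regression to the mean. Randomisation rules that out in expectation, and stratification on fasting C-peptide, GADA titre and BMI should limit imbalance on related endpoints.
- **Scope.** It is tempting to extend the contradiction across all of section 9.4. The sentence beginning "Continuous variables will be analyzed with ANOVA for randomized block design, paired t-test and rank sum test" concerns within-group change, so it does not conflict with the synopsis; only the between-group sentence does. Rank-sum tests appear in 9.4 and not in 9.4.2 or 9.4.4. Section 9.4.4 repeats the one-way ANOVA wording, but the synopsis model covers primary and secondary endpoints only, so the exploratory section contradicts nothing.
- **Contrasts.** One-way ANOVA does not exclude follow-up contrasts with control, and an SAP could name them.
- **Partial cover.** Fasting C-peptide at weeks 26, 52 and 78 is already estimated at each visit within the primary MMRM.

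These replies narrow the point. None of them reconciles the synopsis with 9.4.2 or says which of the two methods within 9.4.2 governs.

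**Conclusion.** The contradiction stands for the continuous secondary endpoints, clearly so for MMTT C-peptide AUC, HbA1c and insulin dose. It should be corrected before analysis. The consequence that follows directly from the 9.4.2 wording is loss of baseline adjustment: 43% to 5% more subjects for equal precision as r goes from 0.4 to 0.9, assuming equal variances at both times. With complete data this is a loss of precision, not of validity. The possible loss of about 20 per 100 subjects per arm applies only if repeated-measures ANOVA is run on complete cases. The omnibus test does not by itself answer the secondary objectives. The primary analysis and the sample size are not affected.

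**What to change.** In 9.4.2, and in the between-group sentence of 9.4, replace ANOVA of change with the synopsis model. Fit it as a likelihood-based repeated-measures model with treatment, visit, treatment-by-visit and baseline value. Report saxagliptin minus control and saxagliptin plus vitamin D3 minus control at each visit. Where a visit is analysed alone, use ANCOVA on the baseline value. The visit terms go beyond the synopsis, which names only treatment and baseline.

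Two further additions are improvements and not corrections:

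- Include the randomisation strata in the model.
- Use the same baseline-adjusted model in 9.4.4 for saxagliptin plus vitamin D3 against saxagliptin.

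If the full analysis set is to be used for secondary endpoints, section 9.3 must be changed at the same time, because it assigns them to the per-protocol set.

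The cost is protocol and SAP wording. Baseline values are already collected, and a model of this type is already specified for the primary endpoint in 9.4.1.

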#### **9.4.3 Analysis method for safety endpoints:**

The incidence of adverse events (AEs) and apparent abnormal central laboratory results will be summarized according to different treatment groups. All severe adverse events and AEs that cause discontinuation from the study will be recorded in detail. All changes of clinical laboratory parameters and vital signs at each scheduled time points from the baseline will be summarized according to treatment groups.

#### **9.4.4 Exploratory analysis**

The exploratory endpoints mainly focus on the add on effects of vitamin D3, so analysis are between vitamin D3 + saxagliptin + metformin (and insulin) group vs. saxagliptin + metformin (and insulin) group, including C-peptide changes during MMTT, HbA1c, FPG, PP and insulin-sparing effects and GADA titers. The relationship analysis of HLA-DQ with therapeutic effects will be applied to all three groups. Measurement data will be presented as mean, standard deviation, median, quartile, maximum value and minimum value. One-way ANOVA will be used to examine the baseline data and the changes in AUC during MMTT, FPG, PPG, HbA1c and insulin dose between groups. The changes of secondary variables describes above from the baseline within the same group will be analyzed with repeated measurement analysis of variance. The frequency counts and percentages will be summarized on proportion of patients achieving  $\beta$ -cell function protection and glycaemic control. Analyses in terms of age, BMI, baseline HbA1c, HLA-DQ genotypes, variations of immune repertoire before and after treatment, gender and other items will be collected.

## **10. STUDY AND DATA MANAGEMENT**

### **10.1 Monitoring of the study**

During outpatient visits of the study, the monitors will have regular contacts with investigators and designated staff by telephone, mail and/or email. Designated monitors will have monitoring visits to each study site. Investigators should allow monitors to

check the clinical, laboratory and pharmacy equipment to ensure not to violate GCP and local regulations. All CRF and corresponding original medical records (source document) will be prepared well in order to be examined in regular inspection for sponsor representatives. During inspection, monitors will verify whether the investigational team is adhering to the protocol and that data are being accurately recorded. All records will be inspected by China Food and Drug Administration (CFDA) and other regulatory agencies

According to ICH E6, Section 1.52, source files include, but are not limited to the following documents:

- According to ICH E6, Section 1.52, source document includes but not limited to following files:
- Outpatient records, visit records and hospitalized records
- Copies of medical records by medical personnel which have been verified for the accuracy.
- Data recorded by automated instrument, for example, X-ray photographs and other reports of imaging examination (such as ultrasonogram, CT scan, MRI and other radiographs), ECG, cardio rhythm graphs, electroencephalogram, polysomnography, pulmonary function test (no matter how these be recorded, including microfilm and photographic plates)
- Questionnaires about pain, life quality and case history by subjects
- Telephone records
- Pharmacy distributive and inventory records by chemists or other study staff
- Laboratory results and other laboratory test results, for example, records of urine pregnancy test and urine indicator paper test
- Messages or memorandum about treatment among doctors for sending to IRB/IEC
- Completed directly by subjects as a part of CRF of self source document (etc. questionnaires).

### **10.1.1 Source data**

The medical record is considered as source material in a clinical trial and should be intact. The data in the Case Report Form derives from source material and should be in accordance with the latter. All observations and examination results in the trial should be recorded timely, accurately, intactly, standardly and factually on the medical record and filled correctly to the CRF. Alteration can not be made casually, if a error appears, correction must not interfere with the original note, name of whom and time should all be signed.

All laboratory data should be recorded during the study, the original report or its copy should be kept together with the research medical record. Data in the normal range should also be recorded in detail, remarkable deviation or clinical unacceptable data should be further verified. All examination results should indicate the unit of measurement.

### **10.1.2 Study agreements**

The investigators at each centre should comply with all the terms, conditions, and obligations of the Clinical Study Agreement. In the event of any inconsistency between this Clinical Study Protocol and the Clinical Study Agreement, the terms of Clinical Study Protocol shall prevail with respect to the conduct of the study and the treatment of subjects.

Agreements between Principal Investigator and CRO and other investigators should be in place before any study-related procedures can take place, or subjects are screened.

### **10.1.3 Archiving of study documents**

After completing the study, investigator should follow the principles outlined in the Clinical Study Agreement (CSA).

## **10.2 Study timetable and end of study**

The end of the study is defined as the last visit of the last subject undergoing the study. The study is expected to start in Q1 2016 and to end by Q2 2019.

The study may be terminated at individual centres if the study procedures are not being performed according to GCP, or if recruitment is slow.

AstraZeneca and principal investigator may also terminate the entire study prematurely if concerns for safety arise within this study or in any other study with saxagliptin.

Upon terminating the study, the Principal Investigator/Investigator will report in writing the completion of the study as well as the summary of the results to the head of the study site in accordance with the study site's rules.

### **10.3 Data management**

During the implement and completion of the study, files of the study data will be stored by each study center. Paper editions of they study data should be stored in a locked cabinet.

The identity of each subject will be coded. Participation in this study is strictly confidential. Any information that is published will not reveal the identity of the subject. All records will be kept at minimum of 15 years by each study center.

#### **Serious Adverse Event (SAE) Reconciliation**

SAE Reconciliation Reports are produced and reconciled with Patient Safety database and/or the Investigational Site.

#### **Management of external data**

The patient's personal data, which are included in the investigator database, shall be treated in compliance with all applicable laws and regulations;

## **11. ETHICAL AND REGULATORY REQUIREMENTS**

### **11.1 Ethical conduct of the study**

This Clinical Trial will be conducted in accordance with the principles laid down by the 18th World Medical Assembly (Helsinki, 1964) and all applicable amendments laid down by the World Medical Assemblies, and the International Conference on Harmonisation

(ICH) guidelines for Good Clinical Practice (GCP). This clinical trial will be recorded in the public registry website [clinicaltrials.gov](http://clinicaltrials.gov) before the enrolment of the first patient. The registry will contain basic information about the trial sufficient to inform interested patients (and their healthcare practitioners) how to enrol in the trial.

## **11.2 Subject data protection**

The patient's personal data, which are included in the sponsor database, shall be treated in compliance with all applicable laws and regulations;

When archiving or processing personal data pertaining to the investigator and/or to the patients, the sponsor shall take all appropriate measures to safeguard and prevent access to this data by any unauthorized third party.

The sponsor also collects specific data regarding investigator as well as personal data from any person involved in the study which may be included in the sponsor's databases, shall be treated by both the sponsor and the investigator in compliance with all applicable laws and regulations.

## **11.3 Ethics and regulatory review**

This Clinical Trial will be conducted in compliance with national laws and regulations, as well as any applicable guidelines. An Ethics Committee should approve the final study protocol, including the final version of the Informed Consent Form and any other written information and/or materials to be provided to the subjects. The Investigator will ensure the distribution of these documents to the applicable Ethics Committee, and to the study site staff. The opinion of the Ethics Committee should be given in writing.

The Ethics Committee should approve all advertising used to recruit subjects for the study.

## **11.4 Informed consent**

The Principal Investigator(s) at each centre will:

Ensure each subject is given full and adequate oral and written information about the nature, purpose, possible risk and benefit of the study

- Ensure each subject is notified that they are free to discontinue from the study at any
- time
- Ensure that each subject is given the opportunity to ask questions and allowed time to consider the information provided
- Ensure each subject provides signed and dated informed consent before conducting any procedure specifically for the study
- Ensure the original, signed Informed Consent Form(s) is/are stored in the Investigator's Study File
- Ensure a copy of the signed Informed Consent Form is given to the subject
- Ensure that any incentives for subjects who participate in the study as well as any provisions for subjects harmed as a consequence of study participation are described in the informed consent form that is approved by an Ethics Committee.

### **11.5 Changes to the protocol and informed consent form**

Study procedures will not be changed without the mutual agreement of the sponsor and AstraZeneca.

If there are any substantial changes to the study protocol, then these changes will be documented in a study protocol amendment and where required in a new version of the study protocol (Revised Clinical Study Protocol). And the sponsor needs to ask approval from AstraZeneca.

The amendment is to be approved by the relevant Ethics Committee and if applicable, also the national regulatory authority approval, before implementation. Local requirements are to be followed for revised protocols. Sponsor will distribute any subsequent amendments and new versions of the protocol to each Principal Investigator(s). If local regulations require, any administrative change will be communicated to or approved by each Ethics Committee. The Investigator(s) may deviate from or make a change to the

protocol without documented agreement between the Principal Investigator and Sponsor only in the event of a medical emergency, e.g., it is only way to avoid an immediate hazard to the subjects. In such case, the Principal Investigator must notify details of the deviation or change, the reason, and a proposed revision in the protocol if required, to Sponsor and the head of the study site and via the head of the study site as soon as possible, in order to obtain their approval. A certificate of approval by the head of the study site as well as sponsor should be obtained

## **12. QUALITY CONTROL AND QUALITY ASSURANCE**

Sponsor and investigator should perform their respective duties and comply with Clinical Trial Protocol to ensure quality control and quality assurance for clinical trial, using Standard Operation Procedure (SOP).

### **12.1 Monitoring**

Monitor will prepared a complete monitoring plan before the initiation of the study, and during the study, the monitoring should be performed according to the monitoring plan. Sponsor is responsible for the monitoring of properly study performing and should ensure the consistency and availability of the data on CRFs by management and observation plan. The major duties of monitoring team are to assist investigators and sponsor to maintain the high quality in the aspects of ethics, scientificity, techniques and laws. In addition, monitoring team should ensure this study is carried out with the compliance of Clinical Trial Protocol, Chinese GCP and SOP.

During the monitoring of this study, the completeness and accuracy of the case record should be ensured, and should be verified with original record with the presence of investigators. The investigator will help with the performance of sponsor. During the monitoring of the study, monitoring team and sponsor will inspect: ICFs, recruitment and follow-up of subjects, the records and reports of SAEs, the distribution of investigational drugs, the protocol compliance for investigational drugs administration and dosing, and the accountability of investigational drugs, concomitant treatment and the quality of data.

